### Data Collection

#### Step 1: Data Collection

The first phase of participant recruitment will take place in collaboration with midwives. In this first phase, the clinical professionals will collect and send the sociodemographic data and email addresses of possible participants (ie, those women who meet inclusion criteria 1 to 6 and have no exclusion criteria) to the FBK researchers, after obtaining informed consent and explaining the study, its purposes, and the need for verification of the characteristics required by inclusion criteria 7 to 9.

Midwives will collect sociodemographic data using a prestructured form. Each woman will be assigned a unique alphanumeric code. The sociodemographic data collection form and the data collected during the study will be stored separately. In addition, data will be pseudonymized to ensure confidentiality.

The parameters requested from pregnant women will be (1) date of birth, (2) expected date of delivery, (3) educational level, (4) occupation, (5) marital status, (6) the number of pregnancies and deliveries, and (7) partner’s occupation, if any.

#### Step 2: Screening

To fulfill the verification of inclusion criteria 7 to 9, the researchers will contact the participants via email and administer the screening questionnaires in Table 1 via the LimeSurvey platform [50]. This platform complies with current data protection requirements and regulations. After the results of the screening questionnaires and the different sociodemographic inclusion criteria have been processed, the women will be contacted again. The following scenarios will open up. First, the participant does not meet the inclusion criteria by manifesting a markedly positive psychological well-being status (stress level, as measured by the K10, <15.9; a general well-being score, as measured by the General Health Questionnaire (GHQ), <3; and a well-being level >80 on the “mental health” scale of the 36-Item Short Form Health Survey (SF-36). In this case, the woman may not be enrolled in the study, and the reasons for exclusion and the results obtained on the screening questionnaires will be returned by the research psychologists only upon the participant’s request. Second, the participant does not meet the inclusion criteria by manifesting a markedly negative psychological well-being status (stress level measured by the K10>29.9 and obtaining a well-being level <30 on the “mental health” scale of the SF-36). Even in the latter case, the woman may not be enrolled in the study, and the reasons for exclusion from the study and the results obtained on the screening questionnaires will be returned by the research psychologists only upon the participant’s request. In addition, indications of territorial services to which to turn for problems that have arisen will be appropriately provided, again only at the participant’s request. This is so that a structured and agreed system of possible access to a territorial service of qualified psychological support can be suggested to the woman concerned, who will provide intake when appropriate. Third, the participant meets the inclusion criteria and is enrolled in the study.

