**Inclusion criteria**
Be pregnantBe in a gestational state between the 14th and the 26th weekBe aged ≥18 yearsHave a smartphone with internet access, be able to download the app, and be able to use itBe a resident of the Autonomous Province of TrentoKnow and understand the Italian languageHave a stress level score, as measured by the Kessler Psychological Distress Scale, between 15.9 and 29.9Have a general well-being score, as measured by the General Health Questionnaire, ≥3Obtain a score on the Mental Health scale of the 36-Item Short Form Health Survey between 30 and 80.

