#### Step 3: Participation

##### Overview

Women who meet the inclusion criteria and provide consent to participate in the study are enrolled in the study. All women who decide to participate in the study will be asked to sign an informed consent after a careful explanation of the study, as described in the Participant Recruitment and Withdrawal section.

Participants will also be asked if they would like to take part in a qualitative interview 2 months after delivery. In case of positive feedback, their telephone number will be collected to facilitate future contact and follow-up interviews. Women who provide consent to this interview will be sent (again via the app) a questionnaire 1 month after the expected date of delivery in which the following will be asked: (1) actual date of delivery, (2) type of delivery, (3) sex of baby, (4) name of baby, (5) mode of breastfeeding, and (6) date and time when the woman wishes to be contacted for the interview.

As shown in Table 1, the psychoeducational intervention involves completing self-report questionnaires delivered at the beginning, during, and at the end of the interaction with ALBA, in addition to the initial screening phase. Completing the instruments takes about 20 minutes. Specifically, 5 questionnaires will be administered at the beginning and 6 at the end of the intervention to investigate stress, self-efficacy, emotional regulation, psychological flexibility, coping strategies, and psychological well-being. None of these questionnaires has diagnostic purposes, so they will not be used to make diagnoses of psychopathology but only to collect descriptive data. Women with psychopathology will be excluded a priori from participation in the study (as defined in the Participant Recruitment and Withdrawal section). Four questionnaires will be delivered during the course to assess the usability and engagement of the woman with the app and ALBA. Specifically, usability questionnaires will be offered at the end of weeks 3 and 6 (ie, the end of the study).

A detailed description of each instrument that will be administered is presented in subsequent sections.

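### The screening scenario that carries support-service information requires two poor scores together, although either one alone excludes a woman

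*Protocol article*

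**What the plan says.** Textbox 1 (Participant Recruitment and Withdrawal) lists three questionnaire-based inclusion criteria as separate items: K10 between 15.9 and 29.9 (criterion 7), GHQ of at least 3 (criterion 8), and "a score on the Mental Health scale of the 36-Item Short Form Health Survey between 30 and 80" (criterion 9). Step 1: Data Collection has midwives refer "those women who meet inclusion criteria 1 to 6 and have no exclusion criteria", after explaining "the need for verification of the characteristics required by inclusion criteria 7 to 9".

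Step 2: Screening then describes three outcomes:

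1. **Positive-side failure.** K10 below 15.9, GHQ below 3 and mental health above 80. The woman is not enrolled; reasons and results are returned if she asks.
2. **Negative-side failure.** She fails "by manifesting a markedly negative psychological well-being status", specified as "stress level measured by the K10>29.9 and obtaining a well-being level <30" on the mental health scale. She is not enrolled; reasons and results are returned if she asks. In addition, "indications of territorial services to which to turn for problems that have arisen will be appropriately provided", again only on request.
3. **Eligible.** She is enrolled.

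Service information is attached to the second outcome only.

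**The concern.** The exclusion rule and the scenario for excluded women use different logic. Every inclusion criterion must be met, so a woman is excluded if K10 is too high *or* mental health is too low. The scenario that says what happens to her next joins the same two cut-offs with *and*.

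A woman with K10 above 29.9 and mental health of 30 or more cannot be enrolled and does not satisfy the second scenario as worded. The same holds for a woman with mental health below 30 and K10 of 29.9 or less. Staff who follow the text literally have no stated basis for giving either woman the service information, although the study has just recorded a markedly poor score for her. The stake is participant care at screening, not the validity of the results.

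**Working it through.** The protocol has no figure to reproduce here. The check sets the inclusion criteria against the scenarios and counts the score combinations each one covers.

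**Inputs**
- Textbox 1: eligible only if K10 is 15.9–29.9, GHQ is ≥3 and mental health is 30–80.
- Step 2, scenario one: K10 <15.9 and GHQ <3 and mental health >80.
- Step 2, scenario two: K10 >29.9 and mental health <30. GHQ plays no part.
- Step 2, scenario three: all criteria met.

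**Negative side only**

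Two yes/no conditions give 2 × 2 = 4 cells. Removing the cell where neither holds leaves 4 − 1 = 3 cells, and each of them excludes the woman.

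| Cell | Excluded by Textbox 1 | Scenario two with *and* | Scenario two with *and/or* |
|---|---|---|---|
| K10 >29.9 and mental health <30 | yes | covered | covered |
| K10 >29.9 only | yes | not covered | covered |
| Mental health <30 only | yes | not covered | covered |
| **Covered** | | **1 of 3** | **3 of 3** |

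**All screening profiles**

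K10 (low, in range, high) × GHQ (<3, ≥3) × mental health (<30, 30–80, >80) gives 3 × 2 × 3 = 18 profiles.

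- K10 >29.9: 2 × 3 = 6 profiles. Mental health <30: 3 × 2 = 6 profiles. Both: 2 profiles. At least one: 6 + 6 − 2 = 10, all ineligible.
- As written, scenario two takes 2 of these 10 and misses 10 − 2 = 8.
- As written, profiles with no scenario: 18 − 1 (eligible) − 1 (scenario one) − 2 (scenario two) = 14. Of these, 8 have exactly one markedly negative score.
- With *and/or* in scenario two: 18 − 1 − 1 − 10 = 6 remain without a scenario. All 6 fail only on the positive side, where no service information is offered.

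**Does the change create a conflict?**

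No. Scenario one as written needs K10 <15.9 and mental health >80 together. The first cannot hold with K10 >29.9, and the second cannot hold with mental health <30, so the widened scenario two does not overlap it.

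**The case against.** The best counter-argument is that the literal reading is not the intended one. The paragraph sets out to verify criteria 7 to 9 and offers what looks like a full three-way split: too well, too unwell, eligible. A strict *and* leaves 14 of 18 profiles outside that split, and scenario one lists its thresholds in the same way, so the brackets may only show the direction of failure. This is plausible. But the text does not say so, and if that is the intention, *and/or* expresses it and the present wording does not.

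Second, the practical loss is small. Information is given only on request, and nothing says that a woman excluded on one score would be refused if she asked. Women with suicidal tendencies, a psychiatric diagnosis or current psychological care are meant to be removed before screening, and Step 3 adds "Women with psychopathology will be excluded a priori from participation in the study". This stands and keeps the point minor. It does not remove it: K10 and SF-36 are first administered at Step 2, so a woman with no known exclusion criterion can still return one markedly poor score there.

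Third, a journal article condenses the full protocol, which may be clearer. That would excuse an omitted detail. Here the article states a rule, and the rule does not match its own inclusion criteria.

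Fourth, the cell count follows from any two-condition *and* against *or* and says nothing about how many women are involved. This is correct, and the count is offered only to show which combinations are missed.

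Finally, scenario one has the same fault, so a change to scenario two alone is partial. That is true of the wording. No support provision depends on scenario one, so the part that matters to participants is closed.

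**Conclusion.** The concern holds, as a minor inconsistency. By the inclusion criteria, either negative cut-off alone excludes a woman; by the screening text, both are needed before the service-information provision applies. Two of the three negative-side combinations therefore fall outside the only scenario that carries it, and nothing else in the article extends it to them.

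This rests on reading *and* literally and on the article alone. The number of women affected is unknown, because no joint distribution of K10 and mental health scores is given. Enrolment, outcomes and analyses are not affected.

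**What to change.** In the second scenario of Step 2: Screening, replace *and* with *and/or*, so that it reads as K10 above 29.9 and/or SF-36 mental health below 30. Every woman excluded on a negative cut-off is then covered by the service-information provision. The on-request condition and the first scenario can stay as they are.

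If the sponsor later chooses to loosen the first scenario to *or* as well, 7 of the 18 profiles would meet both scenarios (for example K10 above 29.9 with GHQ below 3), and the text should then give the negative scenario precedence. The recommended change does not need this.

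The cost is one word, with no added procedure or data collection.

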### Participant Recruitment and Withdrawal

Recruitment will occur within the group of pregnant women between the 14th and 26th weeks of gestation attending the pregnancy care services of the APSS in Trentino.

Midwives from the APSS hospital and territorial service were involved in the study to identify women potentially eligible to participate.

The inclusion and exclusion criteria for women to participate in the study are provided in Textbox 1.

Figure 3 shows a flowchart of the research project procedure.

Inclusion and exclusion criteria.

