**Exclusion criteria**
Patients unable to provide informed consent, which is a prerequisite for participation in the studyInadequate understanding of the Italian languageSubstance addiction or in recovery for 1 yearSuicidal tendenciesDepression or other psychiatric diagnosesWomen undergoing medically assisted procreation (due to the increased risk of anxiety and depressive states, ascertained in the literature)Already being placed, followed, or taken care of on a psychological or psychotherapeutic path at the time of recruitment

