### Ethical Considerations

The ethics committee of the APSS approved this study (17241). This study was approved by the ethics committee of the APSS (17241). Recruited women who meet the inclusion criteria and consent to participate will be enrolled in the research. Participants are enrolled voluntarily and do not receive any form of compensation. Their data are pseudonymized using unique codes, and all analyses will be conducted on aggregated data, ensuring that no individual can be identified or traced.

All women who decide to participate in the study will be asked to sign an informed consent form at the time of enrollment after a careful explanation of the project; its aims; how the data will be collected, managed, and processed; the level of involvement required; and the duration of the research, as well as any confidentiality issues. The woman will also be informed of the possibility of quitting the study at any time she wishes without any explanation and that this option would not impact the quality of care or interfere with her course of treatment.

The study will be explained partially by the midwives. In addition, a video recorded by the research team explaining the study, the purpose, and the woman’s involvement in simple, understandable words will also be available. The participants will be informed of the study’s results through the app.

Regarding data protection, a privacy policy will be provided according to articles 13 and 14 of the Regulation EU 2016/679 of the General Data Protection Regulation, explaining the purposes and legal grounds of the data processing, how the personal data will be collected, their categories, how it will be managed, including the data retention period, the obligations of the data controllers, and the rights of the participants who provide data. Personal data are processed for specific research purposes within the scope of public interest tasks of the data controllers. Informed, freely given, voluntary, and explicit consent will be collected regarding the processing of particular categories of personal data (ie, data concerning health and self-reported behavioral habits in the area of lifestyle health). Moreover, specific consent will be requested regarding the possibility of contacting the participant via telephone to conduct the research interviews.

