These psychological instruments were selected for their widespread validation and adaptation in clinical and psychological research, as well as their relevance for assessing various aspects of mental health and coping in the context of digital health interventions. For example, the Kessler Psychological Distress Scale (K10) is a widely used screening tool for psychological distress, with strong validity across cultures, including Italian culture [45,46]. Furthermore, the Multidimensional Psychological Flexibility Inventory (MPFI) and the Perceived Stress Scale (PSS) are highly relevant for examining psychological flexibility and perceived stress, 2 critical constructs for understanding emotional and behavioral responses in mobile health contexts [47-49], (for detailed description of all questionnaires, refer to Step 3: Participation section).

In the framework of this study, these tools are adopted to assess early signals of potential effectiveness of the intervention while assessing UX and UE.

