The General Self-Efficacy Scale (GSE) [57] is a psychometric instrument designed to assess an individual’s general perception of self-efficacy, that is, confidence in one’s ability to organize and perform the actions necessary to handle potentially stressful or difficult situations. It consists of 10 statements on which respondents must express their level of agreement on a Likert scale ranging from 1 (not true for me) to 4 (exactly true for me). Items on the scale explore various aspects of self-efficacy, such as problem-solving ability, overcoming obstacles, and handling unexpected situations. The total score, obtained by summing the scores of all items, reflects the individual’s overall perceived level of self-efficacy and can range from 10 to 40. The GSE scale was translated into 28 languages. Scholz et al [58] examined the instrument’s psychometric properties in 25 countries, concluding that the construct of perceived self-efficacy is international and that the GSE is an equivalent measure across different cultures. Cronbach α ranged from 0.79 to 0.90. The Italian adaptation of the GSE scale was developed by Sibilia et al [59].

The K10 is a widely used screening instrument to measure psychological distress. Developed by Kessler et al [45], the K10 is a short questionnaire consisting of 10 items that investigate the frequency of psychological symptoms experienced by the individual in the past month, such as nervousness, sadness, fatigue, and feelings of hopelessness. Each question is scored on a 5-point scale, ranging from “not at all” to “all the time.” Total scores can range from a low of 10 to a high of 50, with higher scores indicating a higher level of psychological distress. The Transcultural Mental Health Center also makes available the validated version of this questionnaire in Italian [46].

The MPFI [47] is an assessment tool that measures psychological flexibility on several dimensions. It investigates how people adapt their thoughts and behaviors in response to changing situations and challenges. The MPFI focuses on various aspects of psychological flexibility, including openness to experiences, present-moment awareness, and value-driven action. The 12 dimensions of flexibility and inflexibility (according to the hexaflex model) are assessed through 60 Likert scale items from 1 to 6. The Italian adaptation of the MPFI scale was developed by Landi et al [48].

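### Women who screen as markedly distressed get support-service information only if they ask; it should go, unrequested, to all women not enrolled after screening

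*Protocol article*

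**What the plan says.** The rule is in the Protocol article, Data Collection, Step 2: Screening. Researchers email the women and administer the K10, GHQ and SF-36 online. Then "After the results of the screening questionnaires and the different sociodemographic inclusion criteria have been processed, the women will be contacted again". Three scenarios follow: markedly positive (not enrolled), markedly negative (not enrolled), and eligible (enrolled).

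The markedly negative scenario requires a K10 above 29.9 together with an SF-36 mental health score below 30. For these women the reasons for exclusion and the questionnaire results are returned only if requested. On support, "indications of territorial services to which to turn for problems that have arisen will be appropriately provided, again only at the participant’s request". The next sentence gives the purpose: "so that a structured and agreed system of possible access to a territorial service of qualified psychological support can be suggested to the woman" concerned.

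Other sections give the setting:

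- Recruitment is among women "attending the pregnancy care services of the APSS in Trentino".
- One exclusion criterion is "Already being placed, followed, or taken care of on a psychological or psychotherapeutic path at the time of recruitment".
- Under Ethical Considerations, "The ethics committee of the APSS approved this study".

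**The concern.** A screening step that identifies women in marked distress should make it easy for them to find help. Here the default runs the other way: without a request, the information is not given. Asking is harder for a woman who has not been told her scores or why she was not enrolled. The article's own Introduction names stigma as something that can keep women from seeking psychological support, and a request-only rule relies on exactly that step.

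What is at stake is participant safety. These women are not offered the study intervention. Because women already in psychological care are excluded before screening, they also have no such care in place at recruitment.

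**Working it through.** There is no figure in the plan to reproduce. The check is a reading of the rule against its aim and against the eligibility criteria, plus one small calculation.

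**Step 1: rule against aim.** The aim is that access can be suggested to the woman. The sentence stating it opens by explaining the rule before it, so it is not a separate, unprompted offer. The rule therefore meets the aim for women who ask and does not meet it for those who do not.

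**Step 2: search for an unprompted offer elsewhere.** The eligibility criteria, Ethical Considerations, Step 1: Data Collection, Step 3: Participation and Limitations describe none. The re-contact after screening is planned for the women generally, but the article attaches no service information to it.

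**Step 3: what care is in place.** Step 1 sends forward only women who have no exclusion criterion, so those in psychological or psychotherapeutic care are already out. The women do attend APSS pregnancy care, but the article does not say that screening results are passed back to it.

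**Step 4: who is covered.** Inclusion requires K10 between 15.9 and 29.9, GHQ of at least 3 and SF-36 mental health between 30 and 80. Set against the three scenarios:

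| Screening result | Enrolled? | Scenario | Service information described |
|---|---|---|---|
| K10 >29.9 and SF-36 MH <30 | No | Markedly negative | Only on request |
| K10 >29.9 and SF-36 MH ≥30 | No | None | None |
| K10 ≤29.9 and SF-36 MH <30 | No | None | None |
| K10 <15.9, GHQ <3 and SF-36 MH >80 | No | Markedly positive | None |
| All three within limits | Yes | Enrolled | Not applicable |

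The second and third rows matter for the remedy. These women fail inclusion on a distress cut-off but fall in none of the three scenarios, so a change limited to the markedly negative group would miss them.

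**Step 5: level of distress implied by the K10 cut-off.** The instrument has 10 items on a 5-point scale, and "Total scores can range from a low of 10 to a high of 50, with higher scores indicating a higher level of psychological distress". Each item therefore scores 1 to 5 and totals are whole numbers.

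- Above 29.9 means a total of 30 or more.
- 30 / 10 items = a mean item score of at least 3.0 out of 5.

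Under Secondary Outcome the protocol itself says that "the Kessler Psychological Distress Scale (K10) is a widely used screening tool for psychological distress, with strong validity across cultures", so by its own account a score in this range deserves attention. The calculation describes one of two joint cut-offs; it does not measure harm.

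**Step 6: number affected.** This would be the number screened, times the share markedly negative, times the share who do not ask. The article gives none of the three, so no count or range is offered.

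**The case against.** The best case for leaving the text alone is this. The rule is deliberate and ethics-approved, and it respects a woman's choice about whether to learn her result. The women are in contact with APSS midwives, and research psychologists respond if asked. The wording of the re-contact and of the consent information is not shown, and either may tell her that she can ask. The group is narrow: both cut-offs must be met, and women with suicidal tendencies, depression, other psychiatric diagnoses or current psychological care have already been excluded. The questionnaires are not used diagnostically. Recruitment dates are not given, and with preliminary analysis scheduled for early October 2025 much of the screening may be over.

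Most of this limits the point without removing it. Telling a woman that she may ask still leaves the information dependent on her asking. Ethics approval answers a charge of breach, and none is made here. A service contact needs no diagnosis.

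One part stands in full and shapes the fix: sending the information only to the markedly negative group would signal a result that she has not requested.

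A reader might go further and infer that these women are offered nothing at all, or are left without any care. The documents do not support that. The re-contact text is unseen, and the women remain in pregnancy care.

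**Conclusion.** The point holds as a minor improvement in participant safety. The rule is stated explicitly, so it is not a detail left to a fuller protocol, and it serves its own aim only for women who ask. An easy alternative serves that aim better, using a contact that is already planned. No objective, endpoint, sample size or analysis is affected.

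The conclusion rests on three assumptions: that the word joining the two cut-offs in the negative scenario is meant literally; that the access route mentioned in the text is already agreed with the services; and that some screening is still to come. If screening has finished, the benefit for this study is small and the change belongs in the later randomized trial.

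**What to change.** Remove the on-request condition for the service information only, and widen the recipients. Suggested text: *Indications of territorial services will be included, without a request, in the re-contact of all women not enrolled after screening. Reasons for exclusion and questionnaire results remain available on request, and uptake of any service is left to the woman.*

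The same message should go to every woman not enrolled and say nothing about her scores or state. It then reveals no result, and it reaches the women who fail on one distress cut-off alone.

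The cost is one changed sentence, the agreed service contact added to the re-contact, a line in the consent information and a minor ethics notification. The downside is that some women, including those excluded for markedly positive well-being, receive information they did not ask for.
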